#### 2.9.1. Gonorrhoea Infection Power Calculations

Case–control study: To assess the vaccine effectiveness of 4CMenB on gonorrhoea, assuming 1350 cases of gonorrhoea among 15–19-year-olds in the NT (Australian Bureau of Statistics) over a three year period (i.e., 450 per annum), a ratio of 3 matched controls to 1 case and assuming 50% of the eligible control population vaccinated with a correlation of 0.1, the study has at least 90% power at alpha = 0.05 to detect vaccine effectiveness of at least 20% (i.e., OR = 0.8 or less) and allowing for correlation between cases and controls on basis of 0.2. With this estimated number of cases and controls, the study is adequately powered even if 40% of the eligible population is vaccinated.

Interrupted time series study: A power simulation study that assumed three years of monthly observations post-implementation in each of the vaccinated and unvaccinated groups, constant gonorrhoea counts over time in the unvaccinated group (i.e., ~450/12 = 37.5 cases per month, so µ = 3.62), and a Poisson distribution of counts was conducted. Using the method of Feiveson with 1000 runs, the power to detect a coefficient of −0.008 in the vaccinated group as significant is 0.84 (alpha = 0.05, two-tailed test). This equates to a 9.6% reduction in cases in the vaccinated group relative to unvaccinated group (from 450 to 407 cases p.a.), assuming the two groups are of equal size.

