## 3. Primary Objectives

### 3.1. Evaluation of the Effectiveness of 4CMenB Vaccine against Gonorrhoea in 15 to 19 Year Olds

The primary analysis on vaccine effectiveness (VE) will be performed using a case–control method using controls from the sexually transmitted infections (STI) notification database for chlamydia. A case will be defined as any laboratory confirmed case of gonorrhoea among 15–19-year-olds notified to the CDC. For each case, up to four controls will be randomly sampled from a de-identified dataset of individual records extracted from the Chlamydia notification database of the CDC. Although increasing the number of controls per case increases statistical power, beyond a ratio of four controls per case only small improvements in power are expected [24,25]. A secondary case–control analysis will be performed using controls from the Australian Immunisation register (AIR). For each case, up to 20 controls will be randomly sampled from a de-identified dataset of individual records extracted from the AIR, following restriction of the database to the NT to ensure sampling from the same population. A previous similar study on assessing the effectiveness of the varicella vaccine in Australia has shown maximum precision using 20 controls per case [26]. Controls from both AIR and STI databases will be matched to cases by date of birth ± 4 weeks. Vaccination status of controls will be ascertained from the AIR after selection and vaccination considered valid if received ≥3 months before the date of laboratory confirmation of gonorrhoea in the matched case. This method of control ascertainment has been used previously to assess VE of *Haemophilus influenzae* serotype B, pertussis, varicella and measles vaccines in Australia [26]. Conditional logistic regression models will be generated in Stata to estimate VE.

VE will also be estimated using the screening method for 15–19-year-olds with laboratory-confirmed gonorrhoea within 3 months of receiving two doses of the 4CMenB vaccine. The comparator group will include all 15–19-year-olds in the NT. Using the screening method, VE will be estimated as $1-\frac{PCV(1-PCV)}{PPV(1-PPV)}$ where *PCV* is the proportion of vaccinated MenB cases and *PPV* is the vaccine coverage in the age group being analysed [27]. Vaccine coverage data for each age group will be obtained from the AIR.

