### 4.3. Meningococcal Disease

Evaluation of the vaccine impact and effectiveness of 4CMenB administered to young adults on group B IMD in 14- to 19-year-olds.

Vaccine impact on IMD will be estimated using surveillance data from CDC for laboratory-confirmed IMD cases, comparing six pre-vaccine surveillance years to three post-vaccination years as described above for gonorrhoea. Vaccine effectiveness (VE) will be evaluated using screening and case–control methods as described for gonorrhoea. For the case–control analysis, controls will be selected from AIR (20 controls per case). Controls will be matched to cases by date of birth±4 weeks. Vaccination status of controls will be ascertained from the AIR after selection and vaccination considered valid if received ≥14 days before the date of laboratory confirmation of IMD in the matched case.

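### The screening-method formula in section 3.1 is a ratio of p(1−p) products, not of vaccination odds, so at 40–50% coverage a true effectiveness of 20% comes out as about 1–6%

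*Protocol article*

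**What the plan says.** Section 3.1 adds a screening-method estimate to the case–control analyses of gonorrhoea. The estimator is written out: "Using the screening method, VE will be estimated as $1-\frac{PCV(1-PCV)}{PPV(1-PPV", followed only by closing brackets. PCV "is the proportion of vaccinated MenB cases" and PPV "is the vaccine coverage in the age group being analysed". On the comparator the section says: "The comparator group will include all 15–19-year-olds in the NT".

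Section 4.3 reuses the method for invasive meningococcal disease (IMD), where effectiveness "will be evaluated using screening and case–control methods as described for gonorrhoea". Table 1 lists screening under the other analyses of the first primary objective, and again for group B IMD under objective 11. No other part of the article restates or corrects the formula.

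The planning values come from section 2.9.1. The case–control study is sized "to detect vaccine effectiveness of at least 20% (i.e., OR = 0.8 or less"), "assuming 50% of the eligible control population vaccinated", and the text adds that "the study is adequately powered even if 40% of the eligible population is vaccinated". Section 2.9 expects 40–50% participation.

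**The concern.** The screening method works because the odds of vaccination among cases equal the odds in the source population multiplied by the relative risk. Dividing one odds by the other isolates the relative risk. The printed fraction has the right four terms but multiplies where it should divide. It therefore compares PCV(1−PCV) with PPV(1−PPV), which are binomial variances. That ratio does not estimate a relative risk, and because p(1−p) takes the same value at p and 1−p, it does not reliably carry direction.

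The definition of PCV is a second error in the same sentence: it refers to MenB cases in a section whose outcome is laboratory-confirmed gonorrhoea.

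Section 2.8 makes screening one of two approaches to effectiveness whose agreement or disagreement is to be read as evidence about bias. If the printed formula were coded, the two approaches would disagree for purely arithmetical reasons, and readers would look for confounding to explain it. The error would pass to the IMD analysis. It could also reach the cost-effectiveness results, since section 4.6 runs these under the alternative effectiveness methods.

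**Working it through.** The article reports no numerical screening result, so there is no figure to reproduce. The check feeds a known effectiveness through the printed formula.

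**Inputs.** Effectiveness 20% and coverage 50% and 40% (section 2.9.1); participation 40–50% (section 2.9). Other coverages and effectiveness values are assumptions, added to show the range.

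**Step 1: what the method should return.** Let R1 and R0 be the risks in vaccinated and unvaccinated people. Then

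PCV = PPV·R1 / [PPV·R1 + (1−PPV)·R0], so PCV/(1−PCV) = [PPV/(1−PPV)] × (R1/R0).

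Hence VE = 1 − R1/R0 = 1 − [PCV/(1−PCV)] × [(1−PPV)/PPV].

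**Step 2: the PCV implied by a true VE.** Case odds o = (1−VE) × PPV/(1−PPV), and PCV = o/(1+o).

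**Step 3: the plan's own values, true VE 20%.**

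- Coverage 50%: o = 0.8 × 1 = 0.8; PCV = 0.8/1.8 = 0.4444. Printed: 1 − (0.4444 × 0.5556)/(0.5 × 0.5) = 1 − 0.2469/0.25 = **1.2%**. Odds form: 1 − 0.8/1 = 20%.
- Coverage 40%: o = 0.8 × 0.6667 = 0.5333; PCV = 0.5333/1.5333 = 0.3478. Printed: 1 − (0.3478 × 0.6522)/(0.4 × 0.6) = 1 − 0.2268/0.24 = **5.5%**. Odds form: 1 − 0.5333/0.6667 = 20%.

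**Step 4: the range.** Value returned by the printed formula (the odds form returns the true VE in every cell):

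| Coverage | True VE 20% | True VE 50% | True VE 80% |
|---|---|---|---|
| 20% | 13.2% | 38.3% | 71.7% |
| 30% | 9.5% | 30.8% | 65.4% |
| 40% | 5.5% | 21.9% | 56.7% |
| 45% | 3.4% | 16.8% | 51.2% |
| 50% | 1.2% | 11.1% | 44.4% |
| 60% | −3.3% | −2.0% | 26.0% |

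A true VE of zero is returned as zero at every coverage.

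**Step 5: direction.**

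- At 50% coverage the denominator is 0.25, the maximum of p(1−p), so the printed VE cannot be negative. A true VE of −25% gives o = 1.25 and PCV = 0.5556. The product 0.5556 × 0.4444 is the same as for VE +20%, and the result is again 1.2%.
- The two products are equal when PCV = 1 − PPV, that is when (1−VE) × [PPV/(1−PPV)]² = 1. For VE 20% this gives PPV/(1−PPV) = 1/√0.8 = 1.118, so PPV = 52.8%. Above that coverage a 20% effective vaccine is reported as harmful.
- At 40% coverage, a true VE of −25% gives o = 0.8333 and PCV = 0.4545. The printed value is 1 − 0.2479/0.24 = −3.3%: right sign, wrong size. With PCV = 0.60 the printed value is 0, while the true VE is 1 − 1.5/0.6667 = −125%.

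**The case against.** The strongest reply is that this is a notation slip. The printed terms are those of the odds ratio with two division signs missing, the method is named and referenced, and nothing suggests that anyone meant to use a variance ratio. The signs may have been lost in typesetting or when the text was extracted, and the analysts may well have the right form in their code. This stands as a possibility the article cannot settle, and it makes the figures above conditional on literal use of the formula. It does not remove the need for correction: the text shown has both products intact, no other section gives the odds form, and missing division signs cannot explain why PCV is tied to MenB cases.

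Three further points limit the finding:

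- Screening is a supporting analysis. The primary gonorrhoea result comes from conditional logistic regression with chlamydia controls, and neither it nor its power calculation uses this formula. IMD also has a case–control analysis.
- At or below 50% coverage a protective vaccine keeps a positive sign, although its effect is shrunk. Reversal for a 20% effective vaccine needs coverage above about 53%, beyond the 40–50% anticipated, although section 2.9 calls that range conservative.
- Two-dose coverage may be lower than participation, and the shrinkage is then smaller: 9.5% is returned at 30% coverage and 13.2% at 20%.

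The link to the cost-effectiveness results is an inference, because section 4.6 does not name the screening method.

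**Conclusion.** The concern holds. The formula in section 3.1 is not the screening-method estimator, and its definition of PCV names the wrong disease for that section. If used as printed at the plan's 40–50% coverage, it would return 1.2–5.5% for a true effectiveness of 20%, and 11.1–21.9% for a true effectiveness of 50%. At exactly 50% coverage it cannot signal harm at all.

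These sizes assume that the expression is coded literally and that coverage is as planned. The error itself depends on neither. It affects the screening analyses for gonorrhoea and, through section 4.3, for IMD, and leaves the primary case–control analysis untouched. Whether the unseen analysis plan repeats it is unknown.

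**What to change.** - Replace the formula in section 3.1 with VE = 1 − [PCV/(1−PCV)] × [(1−PPV)/PPV].
- Define PCV by outcome: the proportion of gonorrhoea cases who were vaccinated in section 3.1, and the proportion of group B IMD cases who were vaccinated in section 4.3.
- Check the typeset article, the full protocol, the statistical analysis plan and the analysis code against this form, and correct whichever carry the printed version.

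An optional addition is to fit the estimate as a logistic regression of vaccination status among cases with logit(PPV) as an offset. VE is then 1 − exp(intercept), and the model supplies a confidence interval. The correction does not depend on this.

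The cost is one formula and one definition, plus a check of the code. No new data are needed.

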### 2.9. Sample Size

For ethical and equity reasons, all 14–19-year-olds in the NT in 2021–2022 will be eligible to be offered 4CMenB. The estimated eligible population is 14,077, of whom 5621 or 40% are Aboriginal or Torres Strait Islander (June 2016 estimates). We conservatively anticipate 40–50% participation of this population group and up to 30% non-return at 12 months due to factors such as interstate and intra-territory travel.

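### The screening method defines vaccine coverage by age group without tying it to the date of each case, so roll-out and cohort ageing could bias its effectiveness estimate

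*Protocol article*

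**What the plan says.** Section 3.1 of the protocol article estimates VE against gonorrhoea by the screening method, alongside two case–control analyses. The method compares the proportion of cases vaccinated (PCV) with a population coverage (PPV).

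- PPV "is the vaccine coverage in the age group being analysed".
- Its source is the Australian Immunisation Register (AIR): "Vaccine coverage data for each age group will be obtained from the AIR".
- The reference population is likewise undated: "The comparator group will include all 15–19-year-olds in the NT".
- Cases are described as those with "laboratory-confirmed gonorrhoea within 3 months of receiving two doses of the 4CMenB vaccine".

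Section 4.3 carries the method to group B IMD: "Vaccine effectiveness (VE) will be evaluated using screening and case–control methods as described for gonorrhoea".

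On delivery, section 2.9 says that "all 14–19-year-olds in the NT in 2021–2022 will be eligible to be offered 4CMenB" and "We conservatively anticipate 40–50% participation of this population group". In the case–control analyses of section 3.1, by contrast, a dose counts only if it was given at least 3 months before the matched case's laboratory date.

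**The concern.** The screening method is unbiased under no effect only if PPV is the coverage of the population from which the cases came, at the time they arose. Here coverage moves in two ways. During roll-out it climbs from about zero. After roll-out, vaccinated older adolescents leave the 15–19 band and adolescents who were too young for the offer enter it. An index by age group alone follows neither movement.

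The case–control analyses in the same section handle timing by fixing vaccination status relative to the case date. The screening method has no counterpart.

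Screening is one of the two approaches that section 2.8 sets against each other for triangulation, and section 4.6 feeds the alternative VE estimates into the cost-effectiveness ratios. A screening estimate shifted by the delivery timetable could seem to confirm the case–control result, or to contradict it, for reasons unrelated to protection.

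**Working it through.** The article gives no VE, power or bias figure for the screening method, so there is no stated figure to reproduce. The check below is an illustration.

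**Inputs from the article**
- Final coverage C: 0.40 or 0.50, taking expected participation in section 2.9 as coverage.
- Roll-out within 2021–2022 (section 2.9); no uptake curve is given.
- Validity lag L: 3 months (section 3.1, case–control).
- Dose interval: at least 2 months (section 2.2).
- Three years of cases (section 2.9.1). This is stated for the case–control power calculation, not for screening.

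**Assumptions added**
- Coverage starts at zero and rises linearly over R months, with R = 12 or 24.
- The baseline case rate is constant.
- The case window is 36 months from first offer.
- PPV is set to final coverage C.
- True VE is 0.
- The standard formula applies: VE = 1 − [PCV/(1−PCV)] × [(1−PPV)/PPV].

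**Calculation.** Under no effect, PCV is the mean coverage over the window, C × f, where f = (36 − L − R/2)/36.

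| R | L | f | PCV, C = 0.40 | Apparent VE | PCV, C = 0.50 | Apparent VE |
|---|---|---|---|---|---|---|
| 12 | 0 | 0.833 | 0.333 | 25.0% | 0.417 | 28.6% |
| 12 | 3 | 0.750 | 0.300 | 35.7% | 0.375 | 40.0% |
| 24 | 0 | 0.667 | 0.267 | 45.5% | 0.333 | 50.0% |
| 24 | 3 | 0.583 | 0.233 | 54.3% | 0.292 | 58.8% |

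Lowest cell: 1 − (0.333/0.667) × (0.60/0.40) = 1 − 0.75 = 25%. Highest cell: 1 − (0.292/0.708) × (0.50/0.50) = 1 − 0.412 = 59%.

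With a true VE of 20% the vaccinated odds are multiplied by 0.8. The same two cells then read 1 − 0.8 × 0.75 = 40% and 1 − 0.8 × 0.412 = 67%.

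**Sensitivity (true VE 0, C = 0.40 to 0.50)**
- Window from first offer, 6-month uptake, no lag: 13–15%.
- Window from first offer, 24-month uptake, 5-month lag (two doses 2 months apart plus 3 months): 60–64%.
- Window opening 12 months after first offer, lag 0–5 months: 0–6% with 12-month uptake and 13–29% with 24-month uptake.
- Window opening after a 24-month roll-out, lag 0–5 months: 0–3%.
- Formula exactly as printed, in the lowest and highest cells of the table: 1 − 0.2222/0.24 = 7.4% and 1 − 0.2066/0.25 = 17.4%.

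**Does dating the coverage remove the bias?** Replacing PPV by mean coverage over the window, a simple stand-in for coverage at each case's date, returns 0%, 20% and 40% when those are the true values.

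**Ageing after roll-out.** Suppose the offer closes at the end of 2022. Someone aged 15 at the end of 2024 was 13 at closing, so no 15-year-old at that date was old enough to be offered vaccine. A year later the same holds for ages 15 and 16. Coverage of 15-year-olds therefore falls from its roll-out level towards zero. A figure read at the end of roll-out is too high for later cases and pushes VE up. A figure read late is too low for earlier cases and pushes VE down. No size is attached, because the article does not fix these dates.

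**The case against.** A reader might infer that the plan applies one end-of-roll-out figure to every case and therefore carries a 25–59% bias. The article does not support that. It leaves the date of coverage open, gives no case window for screening and gives no uptake curve. The 25–59% needs every assumption listed above, and under other plausible ones the bias runs from about 0% to 64%.

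Three further objections have weight.
- Section 2.10 refers to a pre-specified analysis plan that is not shown, and it may date the coverage. The authors plainly understand the issue, since they date vaccination in the case–control analyses from the same register.
- The calculation replaces the printed formula by the standard one. It also sets aside the case wording, which read literally admits only people already vaccinated, so that cases from before coverage was reached would never enter.
- Screening appears in Table 1 under other analyses, and section 2.8 itself warns that the approaches will disagree unless all are unbiased.

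These points rule out an unconditional bias figure and limit the importance of the point. They do not make the stated definition adequate. PPV is part of the estimator, the article chose to define it, and the definition is by age group only. Correcting the formula and the 3-month wording would not date it. Starting the window later removes most of the roll-out bias but not the change in coverage by age from cohort ageing.

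**Conclusion.** The point holds in a conditional form. As written, PPV is not tied to the date of the case, while coverage in the 15–19 band changes during and after roll-out. If roll-out cases are set against end-of-roll-out coverage, VE is biased upward. Under the tabulated assumptions a vaccine with no effect could appear about 25–59% effective, which exceeds the 20% VE that section 2.9.1 uses for power. If counting starts only after a 24-month roll-out, that component is roughly 0–3% and ageing in and out of the band remains.

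These sizes illustrate the mechanism and are not properties of the plan. The weakness affects a supporting analysis used for triangulation, and the IMD analysis that copies it. The primary analysis with chlamydia controls is date-anchored and is not touched.

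**What to change.** First correct the printed formula and reconcile the 3-month case wording, since no screening estimate can be interpreted until both are settled. Then:

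1. State the case window for the screening analysis.
2. Define PPV for each case as AIR coverage in that case's birth cohort on its laboratory date. Count a dose as valid under the same lag for the case and for the coverage figure.
3. Estimate VE by logistic regression of case vaccination status with logit(PPV) as offset, or stratify by birth cohort and calendar month. Cases from a cohort and date with zero valid coverage carry no information on VE and drop out, because logit(PPV) is undefined there.
4. Apply the same rule to IMD, using the 14-day lag that section 4.3 states for its case–control analysis.

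The cost is a change of wording and a small amount of extra analysis. AIR is already the source of coverage and vaccination status, and the case–control analyses already need dates of birth and vaccination from it. Nothing changes in recruitment, sample size or the primary analysis.

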### 3.2. Estimation of the Effect of 4CMenB on Carriage of all Neisseria Meningitidis in 14 to 19 Year Olds (12 Months Compared to Baseline)

Carriage prevalence of all *N. meningitidePPs* genogroups detected by PCR at 12 months will be compared with the results obtained at baseline using logistic regression. The difference in carriage at 12 months compared to baseline will be expressed as an odds ratio (OR) with 95% CI. Adjustments will be made for gender, age, smoking, ethnicity, remoteness area, household size (number of persons/room) as available and appropriate.

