#### 2.9.2. Meningococcal Carriage Power Calculations and Impact on Disease

Assuming an overall carriage prevalence at baseline of 6.8% (B Part of it study, unpublished data), a sample size of 5239 is required in order to have 80% power to detect a 20% reduction at 12 months (alpha = 0.05, two-tailed test) or 7011 participants to have 90% power. We will recruit at least 5239 and up to 7011 participants during the study. This calculation incorporates a correlation between the baseline and 12-month measures of 0.25 (‘B Part of It’ study) and 30% loss to follow-up.

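### The carriage sample size is a paired calculation, but the logistic regression named for the carriage analysis does not account for two swabs from the same participant

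*Protocol article*

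**What the plan says.** All places are in the protocol article. Under Study Processes (2.2), every participant has an oropharyngeal swab at visit one and a second at visit three, 12 months later, so the two carriage results belong to the same person.

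Section 2.9.2 gives the sample size for this primary objective:
- "Assuming an overall carriage prevalence at baseline of 6.8"%;
- the aim is "to detect a 20% reduction at 12 months" ("alpha = 0.05, two-tailed test");
- "a sample size of 5239 is required in order to have 80% power";
- "or 7011 participants to have 90% power".

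It adds: "This calculation incorporates a correlation between the baseline and 12-month measures of 0.25", together with 30% loss to follow-up. Section 2.9 expects "up to 30% non-return at 12 months due to factors such as interstate and intra-territory travel".

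Section 3.2 describes the analysis. Carriage "at 12 months will be compared with the results obtained at baseline using logistic regression", reported as an odds ratio with 95% CI and adjusted for a list of covariates. Section 4.2 repeats this for the secondary carriage outcomes. Neither section mentions repeated measures, clustering or pairing, and neither says whether participants without a 12-month swab contribute their baseline swab. Section 3.1, for the matched gonorrhoea analysis, explicitly names the conditional form of logistic regression.

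**The concern.** The sample size takes credit for the positive correlation between a person's two swabs, which makes the change in prevalence more precise than a comparison of two separate groups. The model named for the analysis has nothing in it that uses that correlation. In its plain form, logistic regression of carriage on visit treats every swab as an independent observation. The standard error of the visit effect is then too large, and the study does not deliver the power for which it was sized. Carriage is one of only two primary objectives, and a wide interval around no effect would be harder to interpret.

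The analysis set is a linked question. Pairing is complete only among those who return. If everyone's baseline swab is set against the returners' 12-month swabs, the two sides of the comparison are no longer the same people.

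**Working it through.** **Inputs (Section 2.9.2).** p1 = 0.068. A 20% relative reduction gives p2 = 0.0544 and d = 0.0136. Two-sided alpha is 0.05, the correlation is 0.25 and the loss is 30%.

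**Step 1: reproduce the stated sample sizes.**
- Covariance of the two results: 0.25 × √(0.068 × 0.932 × 0.0544 × 0.9456) = 0.01427.
- Probability positive at both visits: p11 = 0.068 × 0.0544 + 0.01427 = 0.01797.
- Discordant probabilities: 0.068 − 0.01797 = 0.05003 and 0.0544 − 0.01797 = 0.03643. Their sum is pd = 0.08645.
- McNemar formula: n = [1.96 × √pd + z_power × √(pd − d²)]² / d².
- At 80% power n = 3667 pairs, and 3667 / 0.7 = 5238.6. At 90% power n = 4908 pairs, and 4908 / 0.7 = 7011.4.

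These match 5239 and 7011. The two-independent-samples formula gives 4876 and 6526 per time point; divided by 0.7 this is 6966 and 9323, which does not match. The stated sizes are therefore paired.

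**Step 2: independence standard error on complete pairs.**
- Variance per pair assumed by the model: 0.068 × 0.932 + 0.0544 × 0.9456 = 0.06338 + 0.05144 = 0.11482.
- True variance per pair: pd − d² = 0.08627.
- Ratio of standard errors: √(0.11482 / 0.08627) = 1.154, so about 15% too wide.
- Type I error: 2 × Φ(−1.96 × 1.154) = 0.024.
- Power: Φ[(d − 1.96 × SE_indep) / SE_true].

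| Enrolled | Pairs | SE_indep | SE_true | Power, swabs treated as independent | Stated power |
|---|---|---|---|---|---|
| 5239 | 3667 | 0.00560 | 0.00485 | Φ(0.543) = 70.6% | 80% |
| 7011 | 4908 | 0.00484 | 0.00419 | Φ(0.983) = 83.7% | 90% |

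A simulation of the log odds ratio test (200,000 runs per setting) gave 70.7% and 83.8%, type I error of 2.3–2.4% and 95% CI coverage of 97.7%. With a participant-robust standard error, the same simulated data gave 80.1% and 90.2%, with type I error of 5.0%.

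**Step 3: all baseline swabs kept (N at baseline, 0.7N at 12 months, loss unrelated to carriage).**
- Variance assumed by the model: 0.06338/N + 0.05144/(0.7N). The true variance is smaller by 2 × 0.01427/N.
- Power with swabs treated as independent: Φ(0.788) = 78.5% at N = 5239 and Φ(1.257) = 89.6% at N = 7011. Simulating the log odds ratio test (300,000 runs per setting) gave 77.3% and 88.9%. The range is therefore about 77–79% and 89–90%. Simulated type I error was 2.8%.
- With a participant-robust standard error on the same set: 84.9% and 93.3%.

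These are unadjusted calculations; covariate adjustment could move them somewhat.

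**The case against.** The strongest reply is that the article never says the swabs are treated as independent. GEE, random-intercept and cluster-robust models are all forms of logistic regression, so the remedy is compatible with the words in 3.2. The article is condensed, and Section 2.10 refers to a separate analysis plan that is not shown and could specify any of these. The authors evidently knew of the correlation, since they used it in 2.9.2. The contrast with the conditional model in 3.1 is suggestive, but that is simply the usual name for a matched case–control analysis.

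Most of this stands, and it makes the power loss conditional. It does not remove the point. Sections 3.2 and 4.2 do state model, effect measure and covariates, and as stated they do not carry the pairing on which 2.9.2 relies.

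A reader might go further in three ways that the document does not support:
- **That power is simply 71% and 84%.** This holds only if the correlation is ignored and only complete pairs are used.
- **That wrong standard errors endanger a positive result.** With positive correlation the error runs the other way: intervals are too wide and type I error is below 5%.
- **That non-return will produce a spurious fall in carriage close to the 20% target.** If non-returners carried at 1.5 or 2 times the returners' rate, the crude prevalence among returners would be lower by 1 − 1/(0.7 + 0.3 × 1.5) = 13% or 1 − 1/(0.7 + 0.3 × 2) = 23%. Those ratios are assumptions with no figure behind them in the document, and the sum ignores the planned adjustment for ethnicity, remoteness and other covariates. The bias also arises only when all baseline swabs are kept, which is not the set on which power falls to 71% and 84%.

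**Conclusion.** The point holds as an inconsistency between the sample size and the named analysis. The carriage sample sizes are paired; the model in 3.2 and 4.2, read as written, is not. If swabs are analysed as independent, the result is conservative. On complete pairs the standard errors are about 15% too wide, type I error is about 2.4% and power is about 71% and 84% against the stated 80% and 90%. With all baseline swabs kept, power is about 77–79% and 89–90%; the comparison is then also exposed to bias if non-return is related to carriage, of a size that cannot be judged from the document.

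These figures rest on the plan's own prevalence, effect, correlation and loss, and on the correlation being left out of the analysis. The text does not establish that last step beyond its silence. The matter should be fixed, but it is a question of precision and clarity, not of false-positive risk.

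**What to change.** In 3.2 and 4.2, state that carriage will be analysed by logistic regression with participant as the cluster (GEE, or cluster-robust standard errors), visit as the exposure and the covariates already listed. This keeps the odds ratio with 95% CI as the reported measure and, on complete pairs, restores the planned 80% and 90% power.

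In the same sentences, name the analysis set: for example, participants with both swabs as the primary set, with an all-swab analysis as sensitivity. Weighting the all-swab analysis for non-return is optional.

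If the separate analysis plan already says this, it is enough to bring the wording into line. The cost is a few lines of text and a small change to the Stata code. No data collection or sample size changes.
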